### Usual Care

Those randomized to the usual care group will receive no electronic or human reminders for pharmacologic management of delirium throughout their hospital stay. Study participants in the usual care arm may receive haloperidol as part of routine care in the ICU, without restriction on the dose or frequency administered. Of note, study participants will be randomized at the patient level, therefore providers will care for patients enrolled in both intervention and usual care arms of the study, exposing the risk of cross-contamination. Study personnel will continue to visit the patients twice daily to perform delirium, safety, and adverse event assessments.

### Randomization

Following the eligibility and screening assessments, informed consent will be obtained from the participant's legally authorized representative. Randomization of eligible patients providing consent will occur in a 1:1 ratio between intervention and usual care groups. The computerized order entry system (GOPHER) is capable of performing this process and will conduct randomization in random blocks of four to encourage even distribution of patients between the intervention and usual care groups.

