**Methods/Design:**

This is a randomized controlled trial of 428 patients aged 18 and older suffering from delirium and admitted to the ICU of Wishard Memorial Hospital in Indianapolis. Subjects assigned to the intervention group will receive a multicomponent pharmacological management protocol for delirium (PMD) and those assigned to the control group will receive no change in their usual ICU care. The primary outcomes of the trial are (1) delirium severity as measured by the Delirium Rating Scale revised-98 (DRS-R-98) and (2) delirium duration as determined by the Confusion Assessment Method for the ICU (CAM-ICU). The PMD protocol targets the three neurotransmitter systems thought to be compromised in delirious patients: dopamine, acetylcholine, and gamma-aminobutyric acid. The PMD protocol will target the reduction of anticholinergic medications and benzodiazepines, and introduce a low-dose of haloperidol at 0.5-1 mg for 7 days. The protocol will be delivered by a combination of computer (artificial intelligence) and pharmacist (human intelligence) decision support system to increase adherence to the PMD protocol.

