### Enrollment and Eligibility

Patients admitted to the ICU for at least 24 hours will be eligible for screening for the study. Screening measures, further described below, will include a measure of the level of sedation using the Richmond Agitation-Sedation Scale (RASS) [28] and the Confusion Assessment Method for the ICU (CAM-ICU) to evaluate for delirium [29]. Criteria for inclusion in the study consist of: (1) patients admitted to any WMH ICU ward (SICU, PICU, MICU, CCU) for ≥ 24 hours, (2) aged ≥ 18 years, (3) score positive for delirium based on the RASS and CAM-ICU on any day during the ICU stay, and (4) are English-speaking. Patients are excluded for a history of severe mental illness, admission with an alcohol-related delirium, admission for an aphasic stroke, have a history of allergic reaction or contraindication to haloperidol, are pregnant or nursing, or have previously been enrolled in the study.

Patients meeting inclusion criteria will be pursued for informed consent by contacting a legally authorized representative. Figure 1 describes the flow of patients through the screening and enrollment plans of the study. As seen in Figure 1, we anticipate approaching approximately 4700 patients for screening in order to enroll 428 in the randomized controlled trial.

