#### Infrastructure of the Computerized Intervention: The Medical GOPHER Physician Order-Entry System

Since 1984, the Medical GOPHER system, a network of computer workstations, has allowed physician order entry and other direct interactions between computer and physician [33]. The Medical GOPHER system is used by physicians to write all orders at WMH and is linked to the Regenstrief Medical Record System (RMRS). It allows the computer to push information to providers as a CDSS. Furthermore, it can do this at the critical time of clinical decision making, while the physician is initiating an order or recording a diagnosis. The study intervention will utilize the GOPHER system to alert any practitioner entering an order (either original or verbal) for any of twenty medications with definite or strong anticholinergic properties that the patient is enrolled in the study and the medication is not recommended. Additionally, the intervention will provide a list of alternatives to consider depending on the intended use of each particular medication.

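### A constant block size of four, in one hospital with distinguishable arms, makes up to a third of assignments deducible by a fully informed enroller; varying the block size is a cheap safeguard

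*Protocol article*

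**What the plan says.** All references are to the Protocol article.

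- **Ratio and blocks (Randomization).** "Randomization of eligible patients providing consent will occur in a 1:1 ratio between intervention and usual care groups". The order-entry system "will conduct randomization in random blocks of four to encourage even distribution of patients between the intervention and usual care groups". One block size is given. No set of sizes and no stratification factor is mentioned. Consent from the legally authorized representative comes before randomization.
- **Size and setting (Abstract, Methods/Design).** "This is a randomized controlled trial of 428 patients aged 18 and older", all "admitted to the ICU of Wishard Memorial Hospital in Indianapolis".
- **Intervention arm.** A pharmacist reviews orders twice daily (Design and Delivery of the Intervention). An order for a listed anticholinergic triggers an alert "that the patient is enrolled in the study and the medication is not recommended" (Medical GOPHER section). Non-ventilated patients get a scheduled haloperidol order, subject to exclusions (Low-Dose Haloperidol course).
- **Control arm (Usual Care).** "Those randomized to the usual care group will receive no electronic or human reminders for pharmacologic management of delirium throughout their hospital stay". No placebo is described. Because randomization is by patient, "providers will care for patients enrolled in both intervention and usual care arms of the study".
- **Consent (Enrollment and Eligibility).** "Patients meeting inclusion criteria will be pursued for informed consent by contacting a legally authorized representative".
- **Analysis (Data Analysis).** Day-8 severity is analysed by ANCOVA on the baseline score. Coma-free and delirium-free days are compared by a two-sample t-test backed by a Wilcoxon test, with regression on patient characteristics as a further analysis.

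**The concern.** With a constant block of four at 1:1, the fourth assignment in each block is fixed by the first three, and the third is fixed whenever the first two agree. Releasing assignments by computer hides the list, but it does not stop someone working out the next assignment from past ones.

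Several features make such tracking conceivable here. There is one hospital, the arms receive visibly different care, providers are shared, and the block size is published. Consent precedes assignment. A patient qualifies by a positive screen on any ICU day, and a representative has to be reached, so the moment of entry is not rigidly fixed.

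If whoever enrols patients could foresee the arm, entry could come to depend on prognosis. The baseline severity covariate would correct only for the part of that selection carried by the baseline score. The duration outcome is more exposed: its main test has no covariates, and days after a death before day 8 count as not coma-free or delirium-free. A difference in how sick the enrolled patients are would therefore feed directly into it.

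**Working it through.** The article gives no figure for predictability, so there is none to reproduce.

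**Inputs.** Block size 4 and ratio 1:1 (Randomization); N = 428 (Abstract), which is 428/4 = 107 complete blocks. One unstratified list is an assumption, because the article is silent on stratification.

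**Certain knowledge under constant blocks of four.** There are 6 equally likely arrangements of two A and two B. The next assignment is certain when one arm is used up:

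| Position in block | Probability that it is certain | Probability that a count-based guess is right |
|---|---|---|
| 1 | 0 | 1/2 |
| 2 | 0 | 2/3 |
| 3 | 1/3 (first two agree) | 1/3 × 1 + 2/3 × 1/2 = 2/3 |
| 4 | 1 | 1 |

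- Certain: (0 + 0 + 1/3 + 1)/4 = (4/3)/4 = 1/3, or 8 of the 24 positions. Over 428 patients, 428/3 = 142.7 expected.
- Guess (always naming the under-represented arm): (1/2 + 2/3 + 2/3 + 1)/4 = 17/24 = 70.8%. Over 428 patients, 428 × 17/24 = 303 correct, against 214 by chance.

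**A larger constant block.** For size 2m the certain share is 1/(m + 1): 1/4 for size 6 and 1/5 for size 8. Enlarging a constant block helps only a little.

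**Randomly varying blocks.** 400 lists of 428 were simulated. The observer sees every past assignment and knows the set of sizes but not their order, and updates the probabilities after each patient.

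| Block sizes | Known with certainty | Best guess right |
|---|---|---|
| 4 only | 33.3% | 70.8% |
| 4, 6 | about 5.4% | about 69.3% |
| 4, 6, 8 | about 2.4% | about 68.1% |

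With 4, 6 and 8, certain knowledge falls from about 143 patients to about 10 (0.024 × 428). The guessing rate falls by under 3 percentage points (70.8 − 68.1 = 2.7).

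**Imbalance.** The largest possible difference between arms is half the largest block: 2 patients for size 4 and 4 patients for sizes up to 8.

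**The case against.** The strongest reply is that predictability in theory is not foreknowledge in practice. The computer assigns after consent, so no list is exposed. The article does not say who approaches representatives, or whether that person sees earlier assignments in order and knows where blocks begin. The four ICU types might have separate lists; that would leave the one-third share as it is but require tracking each list.

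The arm markers are also imperfect at the bedside. Alerts fire only for listed drugs, some intervention patients get no study haloperidol, usual-care patients may receive haloperidol without restriction, and study personnel visit both arms twice daily. Regression on patient characteristics is planned for the duration outcome, and APACHE II and the Charlson index are collected. Varying the block size also barely slows someone acting on best guesses.

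Most of this stands, and it limits the point to a risk. A reader might infer that concealment is lost in practice, or that staff choose how hard to pursue consent for particular patients. The article supports neither: it says that patients meeting the criteria will be pursued and describes no such discretion. That the trial is open-label is likewise an inference from the care described, not a term the article uses.

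The reply does not remove the risk. Assignment after consent does not prevent deduction from past assignments, and imperfect markers at the bedside do not show that the study team is unaware of the arms. The covariate regression is secondary to the t-test and can adjust only for what is measured.

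**Conclusion.** The point holds as an avoidable weakness in a stated design choice. Under a constant block of four, a fully informed enroller could deduce one third of assignments (an expected 143 of 428) and guess 71% correctly. These are upper limits. They assume that the enroller knows the block size and all earlier assignments in the current block, and that the sentence means permuted blocks of constant size, which is its natural reading. Anyone who knows less can deduce less.

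The calculation measures predictability. It does not show that selection occurred or estimate bias in any outcome. The outcome with least protection is coma-free and delirium-free days. The gain from varying the size is the near-removal of certainty, not of guessing. This is a cheap improvement, not an error that undermines the trial.

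**What to change.** In Randomization, replace the constant block of four with permuted blocks of randomly varying size (for example 4, 6 and 8), and state that the sizes and their order are not disclosed to enrolling staff. If the full protocol already varies the size, correct the sentence in the article.

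The cost is a settings change in a randomization that is already computerised. Maximum imbalance rises from 2 to 4 patients in 428 (per list, if stratified), which is negligible. The order of consent before assignment is already in the text and should stay.

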### Evaluation/Assessment Parameters

#### Primary Outcome

*Delirium Recognition: *In accordance with national guidelines [4], the study will identify delirium by using the RASS and the CAM-ICU on all patients who are admitted directly from the emergency room or transferred from other services to the ICU. Such assessment will be performed after 24 hours of ICU admission and twice daily until discharge from the hospital. As an initial step in conducting the CAM-ICU, the interviewer must assess the patient's sedation status to assure a valid CAM-ICU result. The CAM-ICU was validated using the RASS, and therefore this will be the sedation scale utilized for our study evaluation. RASS has excellent inter-rater reliability among adult medical and surgical ICU patients and has excellent validity when compared to a visual analogue scale and other selected sedation scales [28]. The RASS requires 30-60 seconds to perform with minimal training and has been used by our local ICU team. The RASS is a 10-point scale that reflects the patient level of sedation as determined by their responses to verbal versus physical stimulation. A RASS score of -5 indicates a comatose state with lack of response to verbal or physical stimuli, a score of 0 represents alert and calm, and a score of +4 indicates a state of combative, violent behavior with immediate danger to staff, self, or others. A patient with a RASS score of -3 to +4 will be considered eligible to be assessed by the CAM-ICU to determine the presence of delirium [29].

The CAM-ICU will detect delirium among patients receiving ICU care at both the time of ICU admission and during their ICU stay. The CAM-ICU was chosen because of its practical use in the ICU wards, its acceptable psychometric properties, and based on the recommendation of national guidelines [4,35]. The CAM-ICU score is determined by examining the patient for (a) acute and fluctuating changes in mental status, (b) inattention, (c) disorganized or incoherent thinking, and (d) altered level of consciousness. A CAM-ICU score is considered to be positive if the patient displays both a and b, plus c and/or d. The CAM-ICU diagnosis of delirium was validated against the DSM-III-R delirium criteria determined by a psychiatrist and found to have a sensitivity of 97% and a specificity of 92% [36]. The CAM-ICU has been developed, validated and applied into ICU settings and multiple investigators have used the same method to identify patients with delirium [36-38].

*Delirium Severity: *Since the CAM-ICU does not evaluate delirium severity, we selected the Delirium Rating Scale revised-1998 (DRS-R-98) [39,40] developed by [name] and colleagues. The DRS-R-98 was designed to evaluate the breadth of delirium symptoms for phenomenological studies in addition to measuring symptom severity with high sensitivity and specificity. It has been used in treatment, phenomenological and pathophysiological studies and has been translated into 12 languages. Characteristic symptoms include impairments of attention, short and long-term memory, visuospatial ability and orientation, perceptual and sleep-wake cycle disturbances, abnormalities of language and thought process and content, motor agitation and retardation, and mood lability. The DRS-R-98 is a 16-item clinician-rated scale with anchored items descriptions corresponding to both symptoms and temporal aspects of delirium. The severity scale has 13 items each rated from 0 to 3 where the sum has a maximum of 39 points, with higher scores indicating greater severity of delirium. Three additional items (rated from 0 to either 2 or 3) capture temporal course and attribution to an underlying etiology and when added to the sum of the 13 symptom items produce the DRS-R-98 total score that ranges from 0 to 46. The DRS-R-98 has excellent inter-rater reliability (intra-class correlation 0.97) and internal consistency (Cronbach's alpha 0.94) [39,40].

#### Secondary Outcomes

The study will collect demographic and baseline functional information from the patient's legally authorized representative and/or caregivers. Cognitive function status will be obtained by interviewing the patient's legally authorized representative using the Informant Questionnaire on Cognitive Decline in the Elderly (IQCODE). IQCODE is a questionnaire that can be completed by a relative or other caregiver to determine whether that person has declined in cognitive functioning. The IQCODE lists 26 everyday situations where a person has to use their memory or intelligence. Each situation is rated by the informant for amount of change over the previous 10 years, using a Likert scale ranging from 1-much improved to 5-much worse. The IQCODE has a sensitivity between 69% to 100% and specificity of 80% to 96% for dementia [41].

Utilizing the electronic medical record system (RMRS), we will collect several data points of interest at baseline and throughout the study period. First, RMRS will allow us to collect reason for admission, severity of illness (APACHE II) [42], and the number of comorbid conditions (Charlson Comobidity Index) [43] for each patient enrolled in the study. We will also collect length of stay (both ICU and total hospital stay), mortality rate, and hospital-related consequences. We have previously defined hospital-related consequences to include: the number of patients with documented falls, use of physical restraints, injuries such as pulling out IV lines or urinary catheters, any ordered or observed re-intubation, and pressure ulcers. These will be assessed using the RMRS, direct daily observation, and retrospective review of the electronic medical record. This definition of delirium-related hospital complications has been previously used and published [44,45].

Use of all medications, including focused intervention-related medications (anticholinergics, benzodiazepines, and haloperidol) will be monitored through the GOPHER computerized order entry system, as well as the McKesson medication administration system. The McKesson system is used at the patient's bedside and collects the administration of each medication. Additionally, McKesson is able to monitor medications administered as continuous infusions by documenting start times, stop times, and drip rates throughout the administration period.

In our study an adverse event will be defined as any untoward medical occurrence in a subject without regard to the possibility of a causal relationship. Adverse events will be collected after the subject has provided consent and enrolled in the study. If a subject experiences an adverse event after the informed consent document is signed (entry) but the subject has not started to receive study intervention, the event will be reported as not related to study drug. All adverse events occurring after entry into the study and until hospital discharge will be recorded. An adverse event that meets the criteria for a serious adverse event (SAE) between study enrollment and hospital discharge will be reported to the local IRB as an SAE. If haloperidol is discontinued as a result of an adverse event, study personnel will document the circumstances and data leading to discontinuation of treatment. A serious adverse event for this study is any untoward medical occurrence that is believed by the investigators to be causally related to study-drug and results in any of the following: Life-threatening condition (that is, immediate risk of death); severe or permanent disability, prolonged hospitalization, or a significant hazard as determined by the Data Safety Monitoring Board. Serious adverse events occurring after a subject is discontinued from the study will NOT be reported unless the investigators feels that the event may have been caused by the study drug or a protocol procedure. Investigators will determine relatedness of an event to study drug based on a temporal relationship to the study drug, as well as whether the event is unexpected or unexplained given the subject's clinical course, previous medical conditions, and concomitant medications.

Although haloperidol is widely used in treatment of delirium, it is not approved by the FDA for such use, and its efficacy in such treatment is not clear. Although our study employs a low dose (1.5 mg per day) of haloperidol for a short period of time (seven days), its potential adverse effects of QT prolongation and extrapyramidal symptoms (EPS) will be monitored during the study. The study will monitor for the following movement-related adverse effects daily through patient examination and chart review: dystonia, akathisia, pseudoparkinsonism, akinesia, and neuroleptic malignant syndrome. Study personnel will use the Simpson-Angus [46] and Barnes Akathisia [47] scales to monitor movement-related effects.

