#### Regenstrief Medical Record System at WMH

The computerized Regenstrief Medical Record System (RMRS) is the primary instrument for processing data and monitoring patient and physician activity at WMH. RMRS is a modular system, capable of recording appointments, laboratory, pharmacy, and physician ordering activity. This comprehensive database captures all inpatient and outpatient data by date in a fully coded form, making patient care data readily retrievable. Additionally, RMRS contains death certificate information for registered patients who die in, or outside of, Indiana. The RMRS will be used to evaluate secondary study outcomes such as length of stay and mortality.

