#### Benzodiazepine reduction

Withdrawal of benzodiazepines in intervention patients will follow recommendations from the Society of Critical Care Medicine (SCCM) guidelines regarding the use of sedative and analgesic medications in critically ill patients [4]. Benzodiazepine reduction will occur cautiously but deliberately, with constant communication with the primary medical or surgical team and with close monitoring for intolerable withdrawal reactions. Benzodiazepine dose reductions will be initiated with 20-40% dose reduction on day one, with subsequent reductions of 10-25% every 24 hours as tolerated. Safety and tolerability of the weaning schedule will be evaluated through routine nursing assessments of vital signs and behavior documented every four hours.

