#### Low-Dose Haloperidol course

During the ICU stay, every patient who consents to the study, randomized into the intervention group, and is not under mechanical ventilation will received an order of 0.5 to 1 mg haloperidol every 8 hours via oral or parental route for a total of seven days or until discharge from the hospital. Because of age-related pharmacokinetic differences in metabolism and pharmacodynamic sensitivity, patients under the age of 60 years will be given 1 mg/dose, and those aged 60 years or older will be given 0.5 mg/dose. This low dose of haloperidol is based on the critical analysis of the data from the clinical trials that tested the use of antipsychotics in delirium and the drug metabolism of psychotropics in older adults. This low dose is not intended to replace the sedative regimen used in patients receiving mechanical ventilator.

Intravenous haloperidol use has been associated with a higher risk of cardiovascular adverse outcomes, specifically QT prolongation and Torsades de Pointe. However, in a recent systematic review of case reports of haloperidol-associated arrhythmias, a wide range of haloperidol doses were used prior to the inciting events (2-1540 mg). The onset of most events was typically within minutes to hours following the cumulative doses of haloperidol (range 15 minutes to 5 days). The authors concluded that haloperidol given intravenously appears safe when given in doses less than 2 mg. Patients enrolled in our study will not be given haloperidol if they have: (1) a QT prolongation of 500 milliseconds or above, (2) a history of seizure disorders, or (3) an indication for seizure prophylaxis (i.e., severe stroke or traumatic brain injury) as haloperidol may decrease the seizure threshold [34].

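### Adverse event recording ends at hospital discharge, which can coincide with the last haloperidol dose and may come earlier in one arm

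*Protocol article*

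**What the plan says.** All references are to the protocol article.

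- **Recording window** (Secondary Outcomes): "All adverse events occurring after entry into the study and until hospital discharge will be recorded". An event meeting the SAE criteria "between study enrollment and hospital discharge will be reported to the local IRB as an SAE". No interval after the last dose is given.
- **Treatment period** (Low-Dose Haloperidol course): haloperidol is ordered "for a total of seven days or until discharge from the hospital".
- **Onset of arrhythmia** (same section): most cited events began within minutes to hours "following the cumulative doses of haloperidol (range 15 minutes to 5 days").
- **Benzodiazepine wean** (Benzodiazepine reduction): a 20-40% cut on day one, "with subsequent reductions of 10-25% every 24 hours as tolerated". Its safety is checked by routine nursing assessments.
- **SAE rule after leaving the study** (Secondary Outcomes): "Serious adverse events occurring after a subject is discontinued from the study will NOT be reported unless" an exception applies, namely possible causation by the drug or by a protocol procedure. The SAE definition itself admits only events that the investigators believe the study drug caused.
- **Hypotheses** (end of Background): the intervention is expected to shorten hospital stay, lower mortality to 30 days and reduce hospital-acquired complications.
- **Analysis** (Data Analysis): complications and mortality are compared by logistic regression, with covariates when appropriate.
- **Data source** (Regenstrief Medical Record System at WMH): RMRS "captures all inpatient and outpatient data by date in a fully coded form", holds death certificate data and supplies secondary outcomes.

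**The concern.** A safety window should not close because of something the treatment may change. Here it closes at discharge, which raises two problems.

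First, a harm that appears shortly after the last dose can fall outside the window, because for some patients the last dose and the end of recording are the same event. Second, if the intervention shortens stay as hypothesized, its patients are watched for fewer days. Their adverse event counts, and the proportion with an in-hospital complication, would then be lower even at an identical daily rate. A favourable safety comparison could partly reflect when observation stopped.

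**Working it through.** The plan states no figure for this point, so there is none to reproduce. The check sets the windows side by side and then asks what can be quantified.

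**1. Recording after the last haloperidol dose.** For a patient discharged before the seven days are complete, treatment ends at discharge and so does recording. Time recorded after the last dose is therefore close to 0 days, against a cited onset range of 15 minutes to 5 days. Five days is the extreme of that range. The typical onset of minutes to hours can itself run past discharge if a dose is given shortly before.

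**2. The wean.** The article gives no total length, does not say whether the percentages refer to the starting or the current dose, and does not say that the dose must reach zero. If they refer to the starting dose, the day on which zero is reached is 1 + (100 − first cut)/(daily cut), rounded up:

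- 20% then 10%: 1 + 80/10 = day 9
- 40% then 10%: 1 + 60/10 = day 7
- 20% then 25%: 1 + 80/25, rounded up = day 5
- 40% then 25%: 1 + 60/25, rounded up = day 4

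If they refer to the current dose, zero is never reached. On day 7 the remainder is 0.8 × 0.9^6 = 0.425 of the starting dose at the slowest rate and 0.6 × 0.75^6 = 0.107 at the fastest. A wean could thus be unfinished at discharge, and the article does not say how such a patient would be observed. The 4 to 9 days are derived here under one reading and are not protocol figures.

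**3. How many patients are affected.** Table 1 is the only guide. Weighted by monthly admissions (40, 67, 228; total 335):

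- ICU stay: (40 × 5.96 + 67 × 6.10 + 228 × 3.72)/335 = 4.46 days
- Leaving the ICU for home or another facility: (40 × 0.12 + 67 × 0.14 + 228 × 0.38)/335 = 0.30

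These describe all ICU admissions and ICU stay. The window depends on hospital stay in delirious patients, which is not given. Early discharge is plausible for some patients, but the share cannot be estimated.

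**4. Unequal observation time.** With a constant daily rate r, expected events per patient are r × days observed. Assume, for illustration only, 7 days in one arm and 8 in the other: 7r/8r = 0.875, or 12.5% fewer events with no true difference. For the proportion with at least one event, the ratio is (1 − e^(−7r))/(1 − e^(−8r)), which lies between 0.875 and 1 and is nearest 0.875 when events are rare. The stays and the constant rate are assumptions. The direction is also conditional: the hypothesized lower mortality would lengthen observation in the intervention arm and offset part of the effect.

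**5. What else would catch a late harm.** Death is followed to 30 days. The interim harm tests use the primary analysis methods, which concern delirium over the first 8 days, and days after discharge are counted as free of coma and delirium. The article describes no active search for other events after discharge.

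**6. The SAE sentences.** By definition an SAE must be believed related to study drug. The post-discontinuation exception covers events possibly caused by the drug or by a protocol procedure. The first part covers every SAE as defined, so the restriction removes nothing. The second part names events that the definition does not admit. The two sentences do not fit together.

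**The case against.** The strongest reply is that in-hospital recording is a stated and defensible choice for a short inpatient intervention, and that the full protocol may describe more. The cited arrhythmias came from case reports at 2-1540 mg, most began within hours, and the same section reports that intravenous doses below 2 mg appeared safe. The article specifies no test of adverse event counts. Fewer in-hospital complications because of a shorter stay are also, in part, a real benefit to the patient. All of this stands, and it limits the point to one of moderate weight. It does not remove the main fact: the discharge cut-off is stated outright, and complications have a specified between-arm test with no stated allowance for time observed.

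Stronger readings are tempting, but the documents do not support them:

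- **Patients go home on study treatment with no follow-up.** Haloperidol stops at discharge at the latest. Only an unfinished wean could continue, and the text is silent on that. Mortality is followed to 30 days, so a fatal event would be counted as a death.
- **SAE reporting largely stops at discontinuation.** The rule "Serious adverse events occurring after a subject is discontinued from the study will NOT be reported unless" goes on to exempt events possibly due to the drug, which covers every SAE as defined. It concerns leaving the study, not stopping treatment, so it can apply in either arm. The general recording of adverse events until discharge has no exception for discontinuation.
- **The protocol sets a 9-day wean, or the bias is 12.5%.** The first is one corner of a derived range. The second rests on assumed stays.

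**Conclusion.** The point holds in limited form. Adverse event recording ends at discharge, which can coincide with the last haloperidol dose, leaving about 0 days of recording afterwards against a cited onset that is mostly minutes to hours but extends to 5 days. Because the intervention is hypothesized to shorten stay, comparisons of adverse events and complications could favour it through shorter observation.

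That bias would arise only if stay actually differs between the arms. Its size is unknown, since neither hospital stay in delirious patients nor an adverse event rate is given. The SAE definition and the post-discontinuation exception also need to be reconciled; this is a defect of wording and does not show that reportable SAEs are lost.

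**What to change.** 1. In both arms, add record-based ascertainment of adverse events and SAEs from RMRS to one fixed time after randomization, regardless of discharge or discontinuation. Day 30 is a natural example because it matches the mortality outcome. Use this window for the main between-arm safety comparison.
2. Report in-hospital adverse events and complications per patient-day as well as per patient. The per-patient-day rate supplements the fixed window and does not replace it, because stay is itself a post-randomization outcome.
3. Reconcile the SAE definition with the post-discontinuation exception, so that both state the same scope for study drug and protocol procedures. The definition must be one that can be applied in the usual-care arm if SAEs are to be compared.

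The cost is a protocol amendment, extra abstraction from a database that already supplies outcomes, and a few additional tables. Events treated outside the system would be missed, in principle similarly in both arms. No dose, schedule or clinical rule is affected.
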